### Statistical analyses

We will use the statistical package SPSS for Windows (version 21.0) for the analysis of the data. All analyses will be performed according to the intent-to-treat principle. If participants drop out from the study, the lost values ​​will be imputed using multiple imputation [33].

To analyze the incidence of depressive episodes in each of the measurement times (post-treatment, 1, 3, 6, and 12 months of follow-up), a global χ^2^ test will be performed to compare the three groups. If the differences are statistically significant (*p* < 0.05), pairwise comparisons will be performed using logistic regression. The relative risk and the required number of patients to be treated will be calculated following the formulas proposed by Guyatt et al. [34]. In addition, the time it will take participants to undergo a major depressive episode will be analyzed using a survival analysis. The analysis of the effect of the interventions on the outcome variable ‘depressive symptoms’ will be performed using two-way ANOVA with repeated measures. The analyses related to the effects of moderation or mediation will be carried out as per the recommendations of Baron and Kenny [35]. The model to evaluate moderation will include, as an independent variable, the type of treatment, the moderating potential, and the interaction between the two. An optimal combined moderator will also be sought according to Kraemer’s recommendations [36]. For the analysis of the mediation, we will perform adjustment of three regression equations to assess the effect (1) of the predictor variable (amount of treatment) on the dependent variable (change in depressive symptomatology after the intervention), (2) of the predictor variable in the mediator potential of the predictor variable (change in reinforcement and negative thoughts), and (3) of the mediator potential of the dependent variable, controlled by the predictor variable. Dropouts and adherence to interventions will be analyzed using a χ^2^ test to compare the percentage of dropouts and using an independent *t* test to compare the number of modules completed and the register of the intersessional tasks. Likewise, the level of satisfaction with the interventions will be assessed using the CSQ-8 through a frequency analysis and descriptive statistics, and both active conditions will be compared at post-treatment using an independent *t* test.

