The limitations in both studies included problems of adherence to the interventions. Dropout rates were high, ranging from 14.8% [14] to 31.6% [13]; in the study by Arean et al. [13], 57.9% did not even download the assigned intervention app and the level of compliance with homework assignments was not reported. These issues are fundamental because individuals who leave the intervention show worse results and less satisfaction with the therapy, and when evaluating the efficacy of interventions, high dropout rates can lead to bias due to attrition, limiting the generalizability of the results [15]. In addition, homework completion is a significant predictor of therapy outcomes in various populations and interventions [16], including depression prevention interventions in the caregiver population [17]. This shows that when more homework is completed, the therapy results are better, leading to a greater reduction of depressive symptoms [17]. Complementing the interventions implemented through smartphones with a telephone conference call (TCC) to give feedback could help solve these problems. In behavioral skills training procedures, feedback is specifically defined as delivery of praise for correct performance of a target behavior and further instruction following incorrect performance [18].

The objectives of the present study are to (1) assess the efficacy of a cognitive behavioral intervention for indicated prevention of depression in informal caregivers, administered through a smartphone app (CBIA) with and without TCCs with respect to a care control group, (2) analyze the mediators of change in depressive symptoms, and (3) assess adherence and satisfaction with the interventions. As a central hypothesis, both interventions are expected to significantly reduce the incidence of depressive episodes and depressive symptoms compared to the control group at post-treatment and at 1-, 3-, 6-, and 12-month follow-up. Secondary hypotheses are (1) that the change in reinforcement and in negative automatic thoughts will mediate the effects of both interventions and (2) that the participants receiving CBIA + TCC will show greater adherence and satisfaction with the intervention than those who receive CBIA alone.

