### Sample size

Based on a previous study of indicated prevention of depression in caregivers [9], which involved the same program that will be evaluated in the present study (albeit in person), we estimate that a sample size of 49 participants per group (98 in total) would be sufficient to detect an 18.6% difference in the incidence rates of major depression episodes between the experimental group and the control, assuming a two-tailed test α of 0.05 and a power (1 – β) of 0.80. However, considering an attrition rate of approximately 15% based on studies that have evaluated the use of interventions for the treatment of depression applied through an app [14], we estimate that the number of participants per group should be 58, resulting in a final sample size of 174.

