#### Primary outcome measure: major depression

The presence of a major depressive episode will be evaluated with the Structured Clinical Interview for DSM-5^®^ – Clinician Version (SCID-5-CV; [23]). This provides diagnoses of DSM-5 and must be administered by a clinician. It includes the most common disorders in clinical practice, namely depressive disorder, bipolar disorder, schizophrenia and other psychotic disorders, substance use disorders, anxiety disorders, obsessive-compulsive disorder, post-traumatic stress disorder, attention deficit hyperactivity disorder, and adaptive disorders, and it allows the screening of 17 additional disorders. For the pre-treatment evaluation, the entire interview will be used, while in the following evaluations only the module corresponding to the major depressive episode will be used. This interview has been applied face-to-face and telephonically [24]. Interobserver reliability (Kappa) ranges from 0.70 to 1.00.

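### The primary outcome is tested at five visits, each at p < 0.05, with no primary visit, success rule or adjustment, so the trial-wide error rate is not controlled

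*Protocol article*

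**What the plan says.** The primary outcome is defined without a time point: "The presence of a major depressive episode will be evaluated with the Structured Clinical Interview for DSM-5" (Primary outcome measure: major depression). Table 1 attaches none either. The central hypothesis expects a reduction "compared to the control group at post-treatment and at 1-, 3-, 6-, and 12-month follow-up" (Background), so all five times have equal standing.

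Under Statistical analyses, the plan is "To analyze the incidence of depressive episodes in each of the measurement times (post-treatment, 1, 3, 6, and 12 months of follow-up"), and at each of these times "a global χ^2^ test will be performed to compare the three groups". If that test reaches p < 0.05, "pairwise comparisons will be performed using logistic regression". The same paragraph adds that "the time it will take participants to undergo a major depressive episode will be analyzed using a survival analysis", without saying whether this ranks above, beside or below the five χ² tests.

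The Sample size section rests on one two-group comparison, an 18.6-point difference in incidence, "assuming a two-tailed test α of 0.05 and a power (1 – β) of 0.80". It gives neither the two group rates nor the visit to which the difference applies.

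**The concern.** One primary outcome receives five global tests at the full 5% level plus an unranked survival analysis, and nothing in the article says which result decides the trial. A reader of the eventual report could not tell whether a significant result at, say, 3 months alone was the planned proof of prevention or one favourable result out of six. The gate from the global test to the pairwise tests protects comparisons within a visit but does nothing across visits.

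A statistical analysis plan may exist and add detail. But the primary time point is part of the definition of the primary outcome, and the article itself fixes the threshold at each visit. This is therefore a rule stated on the page, not a detail left for later.

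**Working it through.** **1. The plan's own figure.** 49 / (1 − 0.15) = 57.6, rounded up to 58; 3 × 58 = 174. Both reproduce. The 49 cannot be derived uniquely because the group rates are not given. Rates assumed to fit it are 3.2% versus 21.8% (difference 18.6 points): the pooled two-proportion formula at two-sided α 0.05 and power 0.80 gives 48.4, rounded up to 49. One comparison at α 0.05 is what the size supports.

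**2. Independence benchmark.** Five independent tests at 0.05 give 1 − 0.95⁵ = 0.226. This is only a benchmark, since cumulative incidence at successive visits is strongly correlated.

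**3. Simulation with the correlation included.** Inputs from the article: three equal arms of 58, five visits, a 2-df χ² test at 0.05 at each. Assumptions: the same event rate in every arm; visits at 1.15, 2.15, 4.15, 7.15 and 13.15 months from randomization (about five weeks of modules, then follow-up); events either at constant hazard or front-loaded (40, 55, 70, 85 and 100% of events by the five visits). The article does not say whether later visits count all episodes so far or only new ones among those still at risk, and participants with an episode leave the study (Ethics, consent, and permissions). Both versions were run. The chance of at least one p < 0.05 was:

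| Assumed 12-month rate | Cumulative, constant hazard | Cumulative, front-loaded | New cases per interval |
|---|---|---|---|
| 5% | 10% | 10% | 7% |
| 9% | 12% | 11% | 12% |
| 20% | 15–16% | 13% | 17–18% |
| 30% | 16% | 13% | 19–20% |

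Across rates of 9–30% this is 11% to just under 20%, or 11/5 = 2.2 to 20/5 = 4 times nominal. A single test at 12 months gave 4.6–5.0%. Requiring significance at all five visits gave less than 1%.

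**4. Cost of keeping five confirmatory visits.** With Bonferroni, each test is at 0.05 / 5 = 0.01. At the rates assumed in step 1, n per group rises from 49 to 73, and 73 / 0.85 = 85.9, so 86 after attrition (3 × 86 = 258 in total). With 49 per group, power falls from 0.80 to about 0.59.

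**5. Event counts by visit, conditional.** Suppose the 18.6 points are a 12-month cumulative difference, with the rates from step 1 and both active arms at 3.2%. Average expected events per arm at 12 months are 58 × (0.218 + 2 × 0.032) / 3 = 5.5. At the four earlier visits they are 0.5, 1.0, 1.8 and 3.1 with constant hazard, or 2.2, 3.0, 3.8 and 4.6 if front-loaded, all below 5. With a 20% rate in every arm, only three visits (constant hazard) or one (front-loaded) fall below 5.

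**The case against.** The strongest reply is that the central hypothesis names all five times together. Read as a requirement that every visit be significant, it would be conservative, and no inflation would arise. Also, the α of 0.05 in Sample size is an input to a calculation, not a promise about the whole trial. Both points are fair, and for that reason the inflation is stated only for an any-visit reading. But the article states no success rule either way, so it does not exclude that reading.

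A second reply is that the visits are correlated and that sparse early tests reject less often than 5%. With a 9% rate and constant hazard, the post-treatment test rejects only 1.4% of the time. This is true, and it is already in the simulated figures; it lowers the inflation without removing it.

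A reader might also infer that four of the five tests rest on too few events. The documents do not support that as a fact. They give no group rates, no event timing and no counts by visit. That the difference applies at 12 months is only an inference: Sample size relies on an earlier study that Background ties to 12-month follow-up. Background also reports a significant reduction in incidence at post-treatment for the face-to-face programme, so an early test is not shown to be futile.

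**Conclusion.** The point holds: five unadjusted tests of the primary outcome, an unranked survival analysis, no primary visit and no success rule, in a trial sized for one comparison. Under an any-visit reading the false-positive rate is roughly 2 to 4 times nominal. That range depends on assumed null rates of 9–30%, on assumed event timing and on how incidence is counted; at a 5% rate it is 7–10%. A single figure such as three times nominal is only a mid-range value, and 22.6% would apply only to independent visits. The low event counts at early visits are a conditional warning, not an established defect. Nor do the documents show that 12 months must be the primary visit; that choice belongs to the sponsor.

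**What to change.** Designate one confirmatory analysis of the primary outcome before outcomes are seen. Two options fit the existing plan:

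- Cumulative incidence of a first episode through 12 months: global test at 0.05, then the pairwise tests. With three groups this order protects the three comparisons at that visit.
- The time-to-event analysis already planned, with the test named.

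Report the remaining visits as supportive estimates with confidence intervals. State that incidence is cumulative (or define it otherwise), and give the group rates and the time point behind the 18.6 points.

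The change is to wording in the analysis section and the registration. The sponsor gives up confirmatory claims at the other visits. The 49, 58 and 174 stay as they are; because that calculation is for a difference in proportions, choosing the time-to-event option calls for a short confirmation of its power. If all five visits must remain confirmatory, error has to be controlled across them, at the price shown in step 4 of the working.

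### Mediation is to be judged by the Baron–Kenny steps with no estimate or interval for the indirect effect; if all three steps must be significant, the total-effect step can block real mediation

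*Protocol article*

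**What the plan says.** The Background section of the protocol article states as a secondary hypothesis "that the change in reinforcement and in negative automatic thoughts will mediate the effects of both interventions". Mediation is also the second objective there.

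Statistical analyses fixes the method: "The analyses related to the effects of moderation or mediation will be carried out as per the recommendations of Baron and Kenny". It describes the models in these words: "For the analysis of the mediation, we will perform adjustment of three regression equations to assess the effect". In my notation, the models that follow are:

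- Equation 1: the effect "of the predictor variable (amount of treatment) on the dependent variable (change in depressive symptomatology after the intervention". This is the total effect, c.
- Equation 2: the effect "of the predictor variable in the mediator potential of the predictor variable (change in reinforcement and negative thoughts". I read this as path a, treatment to mediator.
- Equation 3: the effect "of the mediator potential of the dependent variable, controlled by the predictor variable". I read this as path b, mediator to symptoms given treatment.

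The section names no product a·b, no difference c − c′, and no standard error, interval or test for either. It also gives no rule for combining the three results. Sample size rests on incidence of major depression alone: 49 per group is said to be enough "to detect an 18.6% difference in the incidence rates of major depression episodes between the experimental group and the control".

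**The concern.** The hypothesis concerns the indirect effect, so its null is a·b = 0. Equation 1 addresses a different null, that the total effect c = a·b + c′ is zero. In the named causal-steps approach, a significant total effect is the usual first condition. When most of the effect is mediated, c is close to a product of two moderate paths and so is smaller than either. The weakest of the three tests would then decide the question.

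Two things are at stake. A negative answer on the second objective could reflect low power for equation 1 and not an absence of mediation. A positive answer would carry no size or precision for the mediated part.

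**Working it through.** **Inputs.** From Sample size: 49 evaluable and 58 randomised per group, 174 in total, 15% attrition, two-sided α = 0.05. From Statistical analyses: the three equations. The documents give no effect size for symptoms or mediators, so a (in SD of the mediator), b (slope) and c′ (direct effect in SD) are assumed and varied.

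**1. The plan's own figure.** 49 / (1 − 0.15) = 57.6, rounded up to 58, and 3 × 58 = 174. This reproduces. The 49 cannot be confirmed uniquely because only the difference in incidence is given. The pooled formula yields 49 for a lower incidence of about 3.1–3.3%, so it is attainable. Nothing in this calculation assures power for symptom change or mediation.

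**2. Power of equation 1 as a two-arm contrast.** For 80% power, d = (1.960 + 0.842) × √(2/n). This is 0.52 at n = 58 and 0.57 at n = 49. Power = Φ(d/√(2/n) − 1.96). At 58 per arm it is 19%, 37% and 58% for d = 0.2, 0.3 and 0.4.

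**3. One scenario by hand.** Take 58 per arm, a = 0.5, b = 0.4, c′ = 0 and residual SD 1, so that √(2/58) = 0.1857.

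- Path a: Φ(0.5/0.1857 − 1.96) = Φ(0.73) ≈ 77%.
- Path b: SE ≈ 1/√116 = 0.093; Φ(0.4/0.093 − 1.96) ≈ 99%.
- Both paths: about 0.77 × 0.99 = 76%.
- Total effect: d = 0.2/√(1 + 0.4²) = 0.186; Φ(0.186/0.1857 − 1.96) = Φ(−0.96) ≈ 17%.

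Requiring all three therefore cannot exceed about 17%, although a and b are both found about three times in four.

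**4. Simulation** (2,000 trials per row, 58 per arm, residual SD 1). "Three steps" means c, a and b all p < 0.05. "Interval" means that a 95% Monte Carlo interval for a·b excludes zero.

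| a, b, c′ | c | a and b jointly | three steps | interval |
|---|---|---|---|---|
| 0.5, 0.4, 0 | 17% | 74% | 15% | 73% |
| 0.6, 0.4, 0 | 22% | 88% | 21% | 89% |
| 0.6, 0.5, 0 | 29% | 89% | 28% | 88% |
| 0.8, 0.5, 0 | 46% | 98% | 46% | 98% |
| 0.6, 0.4, 0.3 | 76% | 88% | 70% | 88% |
| 0.6, 0.4, −0.2 | 5% | 88% | 4% | 89% |

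With 49 per arm, the first and third rows become 13% vs 66% and 24% vs 87% (three steps vs interval).

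**5. Sensitivity to scaling and direct effect.** With the outcome standardised instead, at 58 per arm, repeated simulations gave these ranges for three steps vs interval:

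- a = 0.5, b = 0.4, c′ = 0: 15–17% vs 73–76%
- a = 0.6, b = 0.5, c′ = 0: 34–36% vs 90%
- a = 0.6, b = 0.4, c′ = 0.1: 42–44% vs 89–90%
- a = 0.5, b = 0.4, c′ = 0.2: 47–50% vs 76–78%
- a = 0.8, b = 0.5, c′ = 0.2: 88–90% vs 99%

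**6. Both mediators active** (equal and independent, standardised outcome, 58 per arm). For a = 0.5, b = 0.4 each, about 50% vs 77%. For a = 0.6, b = 0.5 each, 83% vs 89%. The path through the other mediator enlarges the total effect and appears as a direct effect in a single-mediator regression.

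**7. Continuous predictor** (amount of treatment, N = 174, standardised a = 0.3, no direct effect). For b = 0.3, 23% vs 96%. For b = 0.5, 52% vs 99%. Adding a direct effect of 0.1 to the latter gives 90% vs 97%.

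**8. False positives** (58 per arm). With a = 0, b = 0.5: three steps about 1%, interval 4% (4–6% across runs). With b = 0, a = 0.6, c′ = 0.5: 4% and 5%.

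**The case against.** A reader might infer that the plan declares no mediation whenever equation 1 is non-significant. The text does not say so. It sets no threshold, order of testing or stopping rule for the three equations, whereas for incidence the same section writes its gate out explicitly. The all-three-significant rule comes from the named approach, and every simulated loss depends on it. This part of the objection stands: equation 1 can block a finding, but the document does not show that it will.

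A reader might also infer that the plan has no valid test of mediation. That goes too far. Equations 2 and 3 are paths a and b, and requiring both to be significant is a valid test of a·b = 0. Its power is within about 2 points of the interval's in the table above. This stands too, and it locates the loss in the total-effect condition and in the missing estimate.

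Third, the lowest power figures assume that the second hypothesised mediator is inert and that mediation is complete. The hypothesis claims neither, and step 6 shows how far the gap then shrinks.

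Finally, an interval for an explanatory analysis might be left to an analysis plan. That would answer a silence. Here the article names the method and lists its equations, and an analysis plan written to match would carry the weakness forward.

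**Conclusion.** The point holds as a conditional one. The stated method gives no estimate or precision for the quantity that the hypothesis concerns. If it is applied with all three steps required, it loses power through a test of a different null.

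The size rests on assumed effects. With 58 per arm, one active mediator, small to moderate paths and a direct effect of 0 to 0.2 SD, power is roughly 15–50%, against 72–90% for an interval on a·b. The loss is moderate to small when both mediators act, and small when the total effect is large. It is greatest when a direct effect runs against the mediated one.

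The documents do not support a claim that mediation will usually be missed in this trial. The error is in the conservative direction and concerns a secondary hypothesis; the primary incidence result is unaffected. Whether the predictor should be amount of treatment or randomised group is a separate matter, and the weakness appears with either.

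**What to change.** In Statistical analyses, keep equations 2 and 3. For each mediator, add an estimate of the indirect effect a·b with a 95% bootstrap or Monte Carlo confidence interval, and conclude mediation when that interval excludes zero. State that equation 1 is reported as the total effect and is not a precondition.

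The cost is a few sentences and a short resampling step, with no new data. The Monte Carlo version needs only the two coefficients and their standard errors. The price is a slightly less conservative null rejection when treatment does not move the mediator: about 5% instead of about 1%, which is still the nominal level.

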#### Attention control group (ACG)

Participants in the control group will receive information on depression equal to the CBIA group in duration (five modules), extension, and mode of administration (via a smartphone app). Participants in this group will receive therapeutically inactive information about depression (e.g., what is depression, prevalence, causes, symptoms) and healthy habits.

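### The mediation regressions use an undefined amount of treatment as predictor, whereas the hypothesis is about the effect of each randomized intervention versus control

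*Protocol article*

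**What the plan says.** The Background section of the protocol article states as a secondary hypothesis "that the change in reinforcement and in negative automatic thoughts will mediate the effects of both interventions". The sentence before it says what those effects are: "both interventions are expected to significantly reduce the incidence of depressive episodes and depressive symptoms compared to the control group".

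The Statistical analyses section describes three regressions for mediation:

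- The first links predictor and outcome: "of the predictor variable (amount of treatment) on the dependent variable (change in depressive symptomatology after the intervention".
- The second links that same predictor with the candidate mediators: "of the predictor variable in the mediator potential of the predictor variable (change in reinforcement and negative thoughts".
- The third links mediator and outcome while the predictor stays in the model: "of the mediator potential of the dependent variable, controlled by the predictor variable".

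Amount of treatment is thus the predictor in equations 1 and 2 and the adjustment variable in equation 3. Randomized group is named in none of them, and the term is not defined.

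Two other statements in the same section bear on this. For moderation: "The model to evaluate moderation will include, as an independent variable, the type of treatment, the moderating potential, and the interaction between the two". For the whole analysis: "All analyses will be performed according to the intent-to-treat principle".

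**The concern.** The hypothesis asks whether each intervention, compared with the attention control, works through reinforcement and negative thoughts. The natural predictor is the randomized arm, because randomization then protects two of the three paths, arm to mediator and arm to outcome. Treatment received is shaped by the participant after randomization.

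The article itself gives reasons to expect this behaviour to track prognosis. Its Background reports that people who leave an intervention do worse, that homework completion predicts outcome, and that caregivers often lack time. An association between amount of treatment and change in the mediator or in symptoms could therefore arise from who completes the programme and not from what the programme does. Objective 2 would then be answered by a dose-response association reported as mediation of a randomized effect.

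**Working it through.** The article gives no sample size, power or expected effect for the mediation analysis, so there is no figure to reproduce. The check compares the statements and then illustrates the direction of the consequence.

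**Step 1. Hypothesis against model.** The hypothesis has two contrasts, CBIA versus ACG and CBIA + TCC versus ACG. The model has one predictor, amount. One coefficient per equation yields one indirect effect per mediator, so separate answers for the two interventions do not follow under any coding of a single amount variable.

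**Step 2. What amount could mean.** The treatment quantities that the Outcomes section says will be recorded are modules completed and fulfilment of between-session tasks (Dropout and treatment adherence). Both are observed after randomization.
- If all arms are counted, the control arm has modules too: "Participants in the control group will receive information on depression equal to the CBIA group in duration (five modules". A module count then does not by itself separate control from CBIA.
- If only the active arms are counted, the control comparison is lost. The outcome text mentions recording in the interventions, and the planned comparison of modules is a two-group *t* test; both point this way.
- If control is coded 0, or amount is a graded arm code, part or all of the predictor's variation is randomized. The article states neither coding.

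**Step 3. Consistency within the section.** The moderation model uses type of treatment, so the section has a term for the arm and does not use it for mediation. A predictor that measures treatment received is not an intent-to-treat contrast.

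**Step 4. Illustration by simulation.** The arm size of 58 is from the Sample size section. Everything else is assumed:
- 4000 runs; each regression tested two-sided at 0.05.
- Unmeasured trait *u* (for example motivation) with loading ρ.
- Modules = 3.5 + 1.2 × (ρ*u* + √(1 − ρ²) × noise), rounded and limited to 0–5, with the same distribution in every arm.
- Mediator change = δ × (active arm) + ρ*u* + √(1 − ρ²) × noise.
- Outcome change = −0.5 × mediator change + noise.
- Randomized arm is entered as active versus control, with the same δ in both active arms.

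Share of runs rejecting the predictor-to-mediator path with no intervention effect (δ = 0):

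| Predictor | ρ = 0 | ρ = 0.3 | ρ = 0.5 |
|---|---|---|---|
| Randomized arm | 4.7% | 5.5% | 4.9% |
| Modules, all arms | 5.2% | 21.3% | 89.2% |
| Modules, active arms only | 4.8% | 15.8% | 73.3% |
| Modules, control coded 0 | 4.6% | 7.9% | 23.4% |
| Graded arm code 0, 1, 2 | 4.8% | 5.6% | 5.5% |

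With a true effect (δ = 0.5 SD on the mediator) and no confounding (ρ = 0), the true indirect effect is 0.5 × (−0.5) = −0.25:

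| Predictor | Path rejected | Mean indirect effect |
|---|---|---|
| Randomized arm | 87.9% | −0.252 |
| Modules, all arms | 4.7% | 0.000 |
| Modules, active arms only | 5.4% | 0.000 |
| Modules, control coded 0 | 77.1% | −0.055 per module |
| Graded arm code | 77.2% | −0.126 per step |

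A plain module count can thus suggest mediation where there is none and miss it where it exists. A coding that carries the arm does much better.

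**The case against.** The strongest reply is that amount of treatment is undefined and the article is condensed. Nothing in it ties the term to modules or tasks. It could be a graded code for control, CBIA and CBIA + TCC, since the arms differ in therapeutic content and contact, and the full plan may say so. Control might also be coded 0, which in the simulation lowers the false rejection rate at ρ = 0.3 from 21.3% to 7.9%. This stands in part: the consequence depends on a coding that the article does not give. It does not remove the mismatch. The article names a predictor, the wording differs from that used for moderation, and a single graded or dose variable still gives one combined answer for two interventions.

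A second reply is that Objective 2 speaks of mediators of change in general, which is broader than a randomized contrast. That is true of the objective, but the secondary hypothesis is specific to the effects of both interventions.

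Third, the simulated rates rest on assumed confounding, and the largest need ρ = 0.5. This stands; they show direction and not expected size. Nor does randomizing the predictor protect the mediator-to-outcome path.

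**Conclusion.** The point holds in a limited form. The mediation predictor named in the Statistical analyses section does not match the Background hypothesis. On its likeliest reading it is adherence after randomization, which opens two of the three paths to confounding, conflicts with the section's intent-to-treat statement, and gives no separate indirect effects for CBIA and CBIA + TCC.

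Three stronger readings are tempting but unsupported:
- A reader might infer that the analysis cannot test the hypothesis at all and discards randomization. That depends on a coding the article does not state.
- A reader might infer that mediator and outcome change cover the same period. The article gives no time window for the mediator.
- A reader might infer that the procedure stops if the first regression is not significant. The article cites a mediation method but states no such rule.

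The size of any bias cannot be derived from the article. The primary incidence analysis and the sample size are unaffected; only the secondary mediation objective is at stake. The change should be made.

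**What to change.** In all three mediation equations, replace amount of treatment with randomized arm, entered as two indicators (CBIA versus ACG and CBIA + TCC versus ACG), and report an indirect effect for each. Adjust for baseline EROS, ATQ and CES-D where collected, because the mediator-to-outcome path is not randomized, and state that residual confounding of that path remains possible. Keep amount of treatment only as a labelled exploratory dose-response analysis, with the quantity defined and the handling of the control arm stated.

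A later CES-D assessment as outcome and a bootstrap interval for the indirect effect are optional. Before choosing a later outcome, check the visit schedule for EROS and ATQ, which the article's text does not give, and note that participants who develop a major depressive episode discontinue the study (Ethics, consent, and permissions), so more of the later outcome would be imputed.

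The cost is a change of wording in the analysis section. Randomized arm is known for every participant, and the core change needs no new data or larger sample.
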